### Outcomes

**
*Primary outcome measure.*
** The primary outcome measure of this study is the participant’s time to lesion resolution without any serious complications. Lesion resolution is the first day on which all lesions are resorbed, scabbed or desquamated and mucosal ulcers healed. Lesion resolution is assessed until a maximum of 14 days since the date that the diagnostic sample is taken (for participants who do not receive mpox-specific antiviral treatment) or the day of treatment initiation (for participants who receive mpox-specific antiviral treatment).

**
*Secondary outcomes.*
** Secondary outcome measures evaluate clinical and virologic outcomes. Clinical outcomes are assessed on the basis of:

1. Clinical status on day 14 and day 28 according to a four-point ordinal scale assessed by a physician or a study nurse. The ordinal scale is a) all lesions are resolved and no serious complications, b) active lesions and no serious complications, c) serious complication and/or hospitalization due to mpox, or d) death.2. Evidence of recrudescence or relapse at day 60 and day 180.

*Note:* A "serious complication" is any complication associated with a Serious Advent Event (SAE) that is life-threatening, results in hospitalisation, prolongation of existing hospitalisation, disability, incapacity, or a congenital anomaly; or any other complication that is considered medically significant.

Virologic outcomes in Tier 1 are assessed on the basis of:

1. Change from baseline in mpox virus DNA levels in throat swabs on days 4, 8, 14 and 28.2. Change from baseline in mpox virus DNA levels in blood on days 4, 8, 14 and 28.3. Presence of mpox virus DNA in lesion swabs on days 4, 8, 14 and 28.

The study also assesses the number and type of SAEs, Suspected Adverse Reactions (SARS) and Suspected Unexpected Serious Adverse Reactions (SUSARs) within 28 days of enrolment.

Pregnancy outcomes defined as the final known health status of the mother and child are evaluated in any participants who are pregnant during the course of the study.

**
*Exploratory outcomes in Tier 2 and Tier 3.*
** Further virologic and immunological outcomes are also evaluated in France under this protocol to learn more about viral transmission, humoral and cellular immune responses. The outcome measures are as follows:

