### Recruitment

Participants are enrolled in the study before laboratory confirmation of mpox on the basis of high clinical suspicion or at any time after they receive a positive diagnosis of mpox infection by PCR. From June 2022 to December 2022, new cases were recruited prospectively from participating sites that had been activated. Then, from January 2023, as new cases were rare, patients managed before the start of the study at participating sites or patients from newly activated sites were recruited retrospectively.

Potential participants are identified and approached to participate in this study by their clinical care team at a participating site. Identification may take place using the Site Investigator’s patient register. The Site Investigator must, in all cases, confirm that the potential participant meets the eligibility criteria before proceeding further with the inclusion process. Any patient meeting the inclusion criteria can be enrolled in the study whether they are currently managed or have previously been managed as a mpox case, provided they give their informed consent to participate.

If the potential participant meets all the eligibility criteria, information about the study is provided using the participant information sheet. The participant information sheet can be given in person during a clinic visit, or in the event that the patient is currently being managed as an outpatient and has no upcoming scheduled clinical visit, the information sheet can be sent by post or email, or it can be explained by telephone
(according to the site’s locally approved practices).

The participant information sheet details no less than: the nature of the study; what it involves for the participant; the implications and constraints of the protocol; and any risks involved in taking part. It is clearly stated that the participant is free to withdraw from the study at any time for any reason without prejudice to future care, without affecting their legal rights or their care and with no obligation to give the reason for withdrawal.

The participant is permitted as much time as desired to consider the information, and given the opportunity to question the Investigator, their doctor or other independent parties to decide whether they participate in the study.

Participation is entirely voluntary.

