### Data collection methods

All data are recorded by the clinical and study teams directly on the REDCap (version 13.1.30)
^
9
^ electronic Case Report Form (eCRF) for each timepoint as defined in
Table 1.

**
*Demographics and medical history.*
** Data relating to the participant’s demographics and medical history are collected at baseline. Demographic includes sex at birth and ethnic group. Medical history includes data on comorbidities, results of pregnancy and HIV tests, data on signs and symptoms experienced by the participant between the collection of mpox diagnostic sample and the point of consent, and details of potential AEs and SAEs occurring between the collection of mpox diagnostic sample and the point of consent.

**
*Medical assessments.*
** Medical assessments are undertaken at baseline, and D14, 28, 60, and 180. These assessments can be conducted in person,
*via* video link or telephone. The data collected include the participant’s signs and symptoms, any treatment they may be receiving for mpox, AEs and SAEs details.

**
*Biologic sampling.*
** Baseline samples are the participant’s diagnostic samples that may have been collected under routine care before the participant signed the consent form. Blood* (~0.5ml to 20ml depending on local collection procedures), two lesion swabs and one throat swab are collected at D4*, 8*, 14, 21* and 28 where feasible to do so and permitted under local and national regulations–the asterisk (*) denotes procedures only for hospitalised subject; day 21 and 28 sampling only if day 14 sample is still positive.

Where local capacity limits sample collection, sites should prioritise the collection of D14 and 28 samples. All samples are tested by PCR only conducted in local laboratories in each participating country.

In Tier 2 in France, in addition to the sampling covered in Tier 1, additional samples of mucosa, saliva, anus, urine, semen or vaginal secretions, and blood are collected at baseline, D8, D14, D28, D60 (in case of oral, genital or anal lesion) and D180 (only if sample is positive at D60).

In Tier 3 in France, in addition to the sampling covered in Tier 1 and 2, additional samples of blood are collected at D28, D60 and D180.

Samples in Tier 2 and 3 are tested as in
Table 2.

**Table 2. T2:** Tests by sample type.

TIER	Test	Sample							
		Lesion	Throat	Mucosal lesion	Saliva	Anus	Blood	Urine	Semen or vagina secretion
1	PCR	X	X				X		
1&2	Bacterial STIs detection		X			X	X	X	

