1&2	HIV-RNA quantification						X		X
1&2	MPXV quantification (sPCR) + infectivity assessment (cell culture)	X	X	X	X	X	X	X	X
1&2	MPXV sequencing	X	X	X	X	X	X	X	X
1&2	Humoral immune response characterisation (anti- MPXV antibodies quantification, seroneutralization)						X		
1&2 &3	Cellular immune response characterisation						X		
1&2	Genetic host factors determination + auto-immune antibodies detection						X		
1&2	Tecovirimat pharmacokinetics						X		

HIV, human immunodeficiency virus; MPXV, mpox virus.

Please refer to ‘Additional File 2: Appendix F’ in
*Extended data* for further information on sample processing, analysis and storage in the UK
^
7
^.

**
*Participant self-assessment survey.*
** All participants are asked to complete a self-assessment survey from the point of entry into the study until D180
*via* a secure online questionnaire. The questionnaire, completed
*via* online REDCap survey, captures information about the participant’s signs and symptoms, including lesion status.

For Tier 2 and Tier 3 in France, the baseline self-assessment survey includes an additional social and sexual behaviour questionnaire.

**
*Outcome assessment.*
** During the medical assessment on D14, 28, 60 and 180, the clinical status according to a four-point ordinal scale (see the
*Outcomes* section) is recorded.

For participants who are pregnant at any time during the study, they are followed in the study until their pregnancy outcome is known.

*Note:* As participants can consent to enrol in the study at any point after receipt of a positive PCR result for mpox infection, the eCRF can be completed using existing medical notes and results of samples already taken.

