## Data management

### Source data

Source documents serve as the initial records of data and are used to obtain participants' data for the electronic case report form (eCRF). These source documents encompass a variety of materials such as hospital records (including medical history and medication details summarized into the eCRF), clinical and office charts, laboratory and pharmacy records, diaries, microfiches, radiographs, and correspondence. If the eCRF is the sole place where data is originally recorded without any other written or electronic records, the entries in the eCRF are considered source data.

In this study, primary data collection occurs through two main methods:

(i) Study staff at participating sites complete electronic case report forms on enrolment, during scheduled study visits, daily for in-patients, and whenever laboratory results become available.

(ii) Participants complete an online questionnaire daily during the first 14 days of the study (or while they are in the hospital) and at specific time points (D21, D28, D60, and D180).

The data entered in the electronic case report forms and the online questionnaire are stored in separate REDCap databases.

To ensure data quality, automatic data checks are programmed into the REDCap systems, alerting users during data entry to minimize missing, inconsistent, or erroneous data. Study sites are responsible for reviewing the data entered into the case report forms for their respective participants.

Centralized monitoring of all data collected in the study is conducted by the University of Oxford. This monitoring involves evaluating data compliance with the study protocol and assessing accuracy, as outlined in the study-specific Monitoring Plan. When issues are identified, queries are triggered to be resolved by the respective sites. If any issues are detected in the Participant Self-Assessment data, the study site is notified to communicate with the participant if necessary.

On-site monitoring may be necessary if serious or repeated non-compliance with the protocol is identified through centralized monitoring. Local or regional coordinating centers will carry out this on-site monitoring.

The REDCap database is hosted at the University of Oxford for a minimum of 25 years following completion of the study.

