### Statistical method

**
*Sample size.*
** This is an observational study. We are interested in the effect of any available treatment against mpox used in the cohort and thus defined treatment outcomes (see below). However, due to the observational nature of this study, there is no formal sample size calculation to assess treatment effect. The availability of treatments and prescription rules differ in time and across countries. Any causal inference analysis will account for confounding effects, pre-specified in the statistical analytical plan.

**
*Participant flowchart.*
** The total number of patients and the flowchart of the study will be presented with the number of patients excluded (with reasons for exclusion, and number of patients for each reason), included, receiving any antiviral drugs, lost-to-follow-up and analysed.

**
*Descriptive statistics.*
** Patients’ demographics and baseline characteristics will be described overall and across analysis groups (
*e.g.*, treated with and without tecovirimat), by using, for continuous variables: sample size, mean, standard deviation, median, interquartile range, minimum and maximum; and for categorical variables: sample size, proportion and number of patients in different categories.

The number of missing values, overall and per group, will be reported.

**
*Inferential statistics.*
** Causal inference methods will be used to derive information on the effects of tecovirimat (or other antiviral drugs) on patients’ outcomes (see below) and assessed from a Cox proportional hazard model. Graphics and tables associated to the analysis of each outcome will be fully detailed in the SAP.

**
*Primary outcome.*
** The time to lesion resolution will be summarized for the overall population and stratified by treatment status using Kaplan-Meier curves, median time-to-event, proportion of resolution at D14, and associated 95% confidence intervals (CIs).

**
*Secondary outcomes.*
** For clinical status at D14 and D28, counts and percentages will be presented with their associated 95% CI. The four-point ordinal scale will be used to estimate a proportional odds model. Recrudescence or relapse will be compared between treatment status with a logistic regression model.

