### Statistical method

**
*Analysis population.*
** All eligible participants will be included in the final analysis,
*i.e.*, the final analysis set will be the overall population of enrolled participants (prospective and retrospective, with positive mpox PCR).

**
*Method to account for missing, unused or invalid data.*
** The number, timing and pattern for missing values will be detailed for each outcome measure. For missing primary time-to-event outcome:

The patients who are lost to follow-up or withdrew from the trial and who did not experience the event will be censored at their lost to follow-up or withdrawal datePatients who died before experiencing the event will be censored at day 14If the patient is hospitalized, the event will be censored at hospital discharge day, whereas if the patient is an outpatient, the event will be censored at the last available date in the medical assessment formsIf the outcome is still missing, it will be searched in the Patient Self-Assessment Surveys (PSA)

For the four-point clinical scales at day 14 and day 28, missing data will be imputed by using the last observation carried forward (LOCF) method for “Death” and “All lesions are completely resolved and no serious complications” modalities. Missing outcomes will be searched as done for the primary endpoint.

Endpoints still missing after these recovery steps will remain missing in the analyses.

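### The outpatient censoring rule for a missing resolution date is not limited to D14 or to visits with active lesions, so participants who healed by D14 without a recorded date can be counted as unresolved

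*Protocol article*

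**What the plan says.** The primary outcome is a time to event that needs a calendar day: "Lesion resolution is the first day on which all lesions are resorbed, scabbed or desquamated and mucosal ulcers healed" (Outcomes). The horizon is short: "Lesion resolution is assessed until a maximum of 14 days since the date that the diagnostic sample is taken", or since treatment start for treated participants. The Statistical method section summarises the outcome by Kaplan-Meier curves, a median and the proportion resolved at D14.

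The rules for a missing primary outcome are in the paragraph of that section on missing, unused or invalid data. Participants lost or withdrawn have their own rule. For the others, inpatients are censored at discharge, and "if the patient is an outpatient, the event will be censored at the last available date in the medical assessment" forms. A further item then says that an outcome still missing will be looked for in the self-assessment surveys.

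Three other statements bear on this:

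- Data collection methods: "Medical assessments are undertaken at baseline, and D14, 28, 60, and 180". In Table 1, assessments from D2 to D13 apply only to hospitalised patients or those attending a pre-scheduled visit.
- Same section, outcome assessment: "During the medical assessment on D14, 28, 60 and 180, the clinical status according to a four-point ordinal scale" is recorded. The first level of that scale is all lesions resolved with no serious complications.
- Source data: "Participants complete an online questionnaire daily during the first 14 days of the study". Recruitment adds that from January 2023 "patients managed before the start of the study at participating sites or patients from newly activated sites were recruited retrospectively".

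**The concern.** Right-censoring at a date tells the Kaplan-Meier estimator that the participant was still unresolved up to that date. The outpatient rule takes the date of the last form whatever that form says about lesions, and the last form can be dated D28, D60 or D180. Once the endpoint is cut at 14 days, any such participant is a full-length non-event.

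Missing dates are foreseeable. Outpatients need not be seen by a clinician between baseline and D14, when much of the healing may occur. Retrospective recruits entered after they had been managed, so daily surveys over D1 to D14 are unlikely for them. Because lost and withdrawn participants have a separate rule, the outpatient rule falls mainly on people still in follow-up, whose last form tends to be late.

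At stake is the primary descriptive result. The D14 proportion would be too low and the median too late, and the confidence intervals would not show it. The plan could also contradict itself, with the same participant resolved on the D14 ordinal scale and unresolved in the D14 Kaplan-Meier proportion.

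**Working it through.** The documents state no resolution rate, missing-data rate or power figure, so there is no figure of the plan's own to reproduce. The check is of direction and possible size.

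**Two illustrative outpatients under the literal rule**

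1. Active lesions at D2; D14 ordinal status resolved, no date recorded; last form at D180. Censored at D180, so a non-event through D14. The records show resolution by D14, so this is wrong.
2. Active lesions at D2; no D14 visit; resolved at D28, no date recorded; last form at D180. Again a non-event through D14. The records show only that healing fell between D2 and D28. The value is wrong if healing came by D14 and right if it came later.

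**Closed form**

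Assumed inputs, none from the documents:

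- p: true proportion resolved by D14.
- m: share of participants with no recorded resolution date, missing independently of the healing time, all with a last form at D14 or later.
- r: share of those missing dates recovered from forms or survey.

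Nobody is censored before D14 in this setting, so the Kaplan-Meier estimate at D14 is the fraction with an observed event:

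estimate = p × [1 - m(1 - r)]

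With no recovery (r = 0) this is p(1 - m):

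| p | m = 5% | m = 10% | m = 20% | m = 30% |
|---|---|---|---|---|
| 50% | 47.5% | 45.0% | 40.0% | 35.0% |
| 65% | 61.75% | 58.5% | 52.0% | 45.5% |
| 80% | 76.0% | 72.0% | 64.0% | 56.0% |

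Example: 0.65 × (1 - 0.20) = 0.52. With half recovered, 0.65 × (1 - 0.20 × 0.5) = 0.585. With full recovery the estimate is p.

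**Simulation check**

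A Kaplan-Meier simulation used 400,000 participants, Weibull times with shape 2 scaled so that a proportion p resolve by D14, and last forms at D28, D60 or D180. It agreed with the closed form to within about 0.001. For p = 65% it gave 0.618, 0.586, 0.521 and 0.455 at m = 5, 10, 20 and 30%. The median moved from day 12 to day 13 at m = 10% and to day 14 at m = 20%, and was not reached by D14 at m = 30%. With the last form at D1 to D3 instead, p = 65% and m = 20% gave 0.646. The bias therefore comes from censoring dates at or after D14.

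**Does censoring at the last visit with active lesions repair it alone?**

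Take p = 65% and m = 20%. Participants truly unresolved at D14 (35%) are seen active then and stay in. Those who healed by D14 without a date (0.65 × 0.20 = 13%) are censored early and effectively drop out. The estimate is about 0.52 / (0.52 + 0.35) = 0.52 / 0.87 = 60%, still below 65%. This censoring depends on the outcome, so it is not enough by itself.

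**The case against.** The strongest case against is that the literal reading is the least favourable one. The endpoint is assessed only to 14 days, so the last available assessment could be taken as the last one inside that window. The rule applies only when the outcome is missing; if the event date were taken from the first form showing resolution, someone seen healed at D14 would have an event and never reach the rule. The closing sentence of the paragraph calls these items recovery steps, which suggests that the survey is meant to rescue outcomes. D14 is a priority timepoint, and the article leaves data handling details to the SAP.

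Part of this stands. The SAP may settle the order of steps and how the date is derived. But the article states a definite rule, places no D14 limit on it, does not say that form status supplies the date, and puts the survey after censoring. Capping the date at D14 would not help either: a participant healed by D14 and censored at D14 is still a non-event.

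Three stronger readings are tempting and are not supported:

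- A reader might infer that everyone later seen healed is misclassified. Participants first healed after D14 are correctly non-events at D14.
- A reader might take the relative bias to equal the share of missing dates. That is the worst case, with every affected participant having a late form and nothing recovered.
- A reader might conclude that the treatment comparison is biased. That requires missingness to differ by treatment status, and nothing in the document shows that it does.

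**Conclusion.** The point holds in a limited form. As written, the rule turns some participants who healed by D14 into non-events: those with no date derivable from forms or survey and a last form at D14 or later. For this group the error always runs towards less and later resolution, and it can contradict the D14 ordinal status.

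The size cannot be fixed from the document. It runs from zero with full recovery to a worst-case estimate of p(1 - m); at an assumed p of 65%, that is a loss of 6.5 percentage points at m = 10% and 13 points at m = 20%. These figures rest on assumed p and m and on missing dates being unrelated to healing time. Any effect on the Cox comparison remains conditional. The rule should be corrected before analysis because it governs the primary endpoint.

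**What to change.** Replace the outpatient rule, in the protocol or the SAP, with an ordered procedure:

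1. Search all sources before any censoring, including the self-assessment survey and the lesion status recorded at D14 and D28. A participant whose D14 form records resolution counts as resolved by D14 in the D14 proportion.
2. Where resolution is recorded without a date, treat the time as interval-censored between the last record of active lesions and the first record of resolution. Do this at least as a sensitivity analysis to the planned Kaplan-Meier and Cox analyses.
3. Where no resolution is recorded, censor at the last assessment with active lesions, at D14 at the latest. Participants recorded as active at or after D14 are censored at D14.

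Step 3 must not be adopted without step 2, because of its dependence on the outcome. Reporting the number of missing dates by treatment status, and how many each source recovered, would show whether the treatment comparison is affected.

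The cost is a short text change, extra programming for the interval-censored analysis, and slightly wider intervals because unknown time no longer counts as observed. No new data collection is proposed, although records completed from existing notes may lack some of the lesion-status dates.

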## Introduction

### Background and rationale

Mpox (formerly Monkeypox) is an acute viral disease caused by the human mpox virus (hMPXV), a member of the Orthopoxvirus family for which there are two distinct genetic clades, Clade I and Clade II
^
1,
2
^. Clade I is associated with higher morbidity and a case fatality rate of approximately 11%
^
3
^ and circulates primarily in parts of Central Africa. Clade II consists of two sub-clades–Clade IIa, historically detected in parts of West Africa (case fatality rate 0–4%
^
3
^), and Clade IIb, identified during the global outbreak starting in May 2022–sometimes also referred to as clade III
^
4
^.

The typical clinical features of human mpox closely resemble those of smallpox, although mpox is considered to be a milder disease. Clinical features of mpox are highly variable, but typically include distinctive centrifugal skin lesions, lymphadenopathy (which is not present in smallpox), fever, and other non-specific symptoms. However, in the 2022 clade IIb outbreaks, which mostly affected men who have sex with men
^
5
^, the clinical presentations differed from those described for cases in previous mpox outbreaks elsewhere. For example, 2022 clade IIb outbreak cases often presented with systemic symptoms typical for mpox, but with highly regional and sometimes more severe lesions, including oropharyngeal, genital, peroneal (peri-anal and ano-rectal lesions), frequently associated with other sexually transmitted diseases. Additionally, the incubation period was shorter (nine days compared to 13 days; range three to 34 days) for clade IIb outbreak cases, and the case fatality rate (CFR) was lower (
<0.01%) compared with the CFR previously reported for Clade II outbreaks in Africa [1.7–6.8%]
^
3
^.

The antiviral agent tecovirimat is the only mpox treatment licensed recently in Europe by the European Medicines Agency (EMA, in January 2022) and by the UK Medicine and Healthcare products Regulatory Agency (MHRA, in July 2022).
Approval was granted under ‘exceptional circumstances’, based on experimental and human safety data, but no clinical efficacy trial had been performed at that time. Tecovirimat, and the unrelated antiviral brincidofovir, are licenced for treatment of smallpox by
US Food and Drug Administration (FDA) under the ‘animal rule’.

The unprecedented 2022–23 international outbreak of clade IIb mpox is associated with over

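### On the four-point scale only resolved and death are carried forward, so retention of a missing status, mainly at D28, depends on the outcome and tends to overstate the proportion resolved

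*Protocol article*

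**What the plan says.** The Outcomes section defines four categories: a) all lesions resolved without serious complications, then "b) active lesions and no serious complications, c) serious complication and/or hospitalization due to mpox, or d) death". Under Statistical method, "For clinical status at D14 and D28, counts and percentages will be presented with their associated 95% CI", and "The four-point ordinal scale will be used to estimate a proportional odds model".

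The missing-data paragraph of the same part states that, for this scale, "missing data will be imputed by using the last observation carried forward (LOCF) method for" two categories: death and "All lesions are completely resolved and no serious complications". Categories b and c are not named. The paragraph goes on: "Missing outcomes will be searched as done for the primary endpoint". For the primary endpoint that search extends to the participant self-assessment surveys. It closes with: "Endpoints still missing after these recovery steps will remain missing in the analyses".

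**The concern.** Whether a participant with no D28 status enters the analysis depends on the status last seen. Someone last seen resolved is always counted, as resolved. Someone last seen in category b or c, with nothing recovered, leaves the denominator. Death is also carried forward but hardly offsets this: the background section says that "for clade IIb outbreak cases, and the case fatality rate (CFR) was lower" than in earlier African outbreaks, at <0.01%.

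Two results are at stake: the reported percentages on the scale, and the proportional odds estimate if it is used to compare treatment groups, which the stated interest in treatment effects suggests. Unequal missingness between groups is plausible. Inpatients are assessed daily until discharge, and retrospectively enrolled participants are completed from existing notes. Only 55 + 7 + 2 = 64 of the 601 enrolled received an antiviral, so the comparison has little room for avoidable bias.

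**Working it through.** The article states no resolution rate, missingness rate or sample-size calculation, so there is no planned figure to reproduce. The rates below are assumptions for D28. Only N = 601 and the fatality figure come from the article.

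**Notation.** r = share last seen resolved. q = chance that a participant last seen not resolved is resolved by D28. m = share of those last seen not resolved who are still missing after the search. Deaths are taken as 0; a death share of 0.01% changes no figure at the precision shown. Resolution is assumed to persist, and missingness to depend only on last status.

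**Formulas.**
- True proportion: P_true = r + (1−r)q.
- Under the stated rule: P_plan = [r + (1−r)(1−m)q] / [r + (1−r)(1−m)].
- Difference: P_plan − P_true = r(1−r)m(1−q) / [1 − (1−r)m].

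The difference is positive whenever m > 0, q < 1 and 0 < r < 1. It does not depend on how many of the resolved are missing, because all of them are filled in.

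**Central case** (r = 0.6, q = 0.7, m = 0.3).
- P_true = 0.6 + 0.4×0.7 = 88.0%.
- P_plan = (0.6 + 0.4×0.7×0.7) / (0.6 + 0.4×0.7) = 0.796/0.880 = 90.5%, an excess of 2.5 points.
- In 601 participants, about 361 last seen resolved all stay, and about 72 of the 240 others leave (601×0.4×0.3).
- Complete-case analysis with the same 30% missing in both strata gives 88.0%, so in that setting the selective fill-in itself creates the bias.
- Carrying every category forward gives 0.6 + 0.4×0.7×0.7 = 79.6%, which is 8.4 points too low.

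**Range.** Over r = 0.4 to 0.8, q = 0.5 to 0.9 and m = 0.1 to 0.4, the rule overstates in every cell. Selected cells:

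| r | q | m | True % | Rule % | Excess (points) |
|---|---|---|---|---|---|
| 0.8 | 0.9 | 0.1 | 98.0 | 98.2 | +0.2 (smallest) |
| 0.4 | 0.9 | 0.4 | 94.0 | 95.3 | +1.3 |
| 0.6 | 0.7 | 0.3 | 88.0 | 90.5 | +2.5 |
| 0.6 | 0.5 | 0.4 | 80.0 | 85.7 | +5.7 |
| 0.4 | 0.5 | 0.4 | 70.0 | 76.3 | +6.3 (largest) |

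**Effect of the search.** Start from 30% missing before the survey search and let it recover a random share of those last seen not resolved. Recovery of 50% (m = 0.15) leaves 0.838/0.940 = 89.15%, an excess of 1.15 points. Recovery of 75% leaves 0.56 points, and 100% leaves 0.

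**If missingness depends on healing.** Let the missing participants resolve with probability q_m instead of q. The true value becomes 0.6 + 0.4×(0.7×0.7 + 0.3×q_m) = 0.796 + 0.12×q_m. This equals 90.5% at q_m of about 0.90. At q_m = 1 it is 91.6%, and the rule is then 1.1 points too low.

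**Group comparison with no true effect.** With m = 0.1 in treated and 0.3 in untreated participants, the rule gives 0.852/0.960 = 88.75% and 90.45%. The odds ratio for resolved, treated against untreated, is about 0.83. With the two rates swapped it is 1.20. This is the ratio for resolved against not resolved, not a fitted proportional odds estimate.

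**The case against.** The other side has several good points.

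- **The search.** A reader might infer that everyone last seen with active lesions is simply dropped. The paragraph does not say that: records and surveys are searched, and only what is still missing stays out. The surveys are daily for 14 days and then at D21, D28, D60 and D180, and they capture lesion status. This stands as a real mitigation. It is not a cure unless recovery is complete, and the article itself expects values to remain missing. The scale is also meant to be assessed by a physician or study nurse, which a survey is not.
- **D14.** A reader might infer that the D14 percentages are inflated to the same degree. The schedule does not support this. The first scheduled outcome assessment is D14, and assessments on D2 to D13 are for inpatients or those with a pre-scheduled clinic visit. Where no earlier status exists there is nothing to carry forward, and D14 is close to a complete-case analysis.
- **Direction.** Participants last seen active may have stopped attending because they healed. The bias could then vanish or reverse. The reversal needs about 90% resolved among the missing in the central case, which the data at hand could not test.
- **Rationale.** Resolved and death are nearly absorbing states, and active lesions should not be assumed to persist. Carrying the first two forward is therefore sensible. The fault is leaving the others missing beside it.
- **Deferral to the SAP.** The absence of an imputation model or a sensitivity analysis from the article is no defect. The article also already promises missing counts by group and their timing and pattern. The point rests only on the rule that the article does fix.

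**Conclusion.** The stated rule makes retention depend on the outcome. When missingness depends only on last status, it overstates the proportion resolved. The effect is mainly at D28; at D14 it arises only where earlier inpatient or clinic records exist. In the central assumed case it is 2.5 points with no recovery and less with recovery, and across the assumed range it is 0.2 to 6.3 points. Where nearly all participants last seen active heal by D28 (q = 0.9) it is at most 1.3 points. A spurious odds ratio of about 0.83 or 1.20 needs unequal missingness by treatment status, which is plausible but not documented.

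Confidence is high in the mechanism and low in the size, because every rate is assumed. The direction is conditional, not certain. A reader might also infer that the study's main result is compromised. That does not follow: this is a secondary outcome in a primarily descriptive study, and the primary time-to-event outcome has its own censoring rules. The change should be made, but it is not critical.

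**What to change.** Keep the search of records and surveys, and keep the carry-forward of death and resolved. For participants still missing after that (last seen in category b or c, or never seen), replace leaving them missing with multiple imputation of the four-point status. The imputation model should use last status and its day, baseline severity, HIV status, recruitment mode (prospective or retrospective) and treatment. Do not extend LOCF to all four categories as the main analysis, since that biases the other way.

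Add a sensitivity analysis that sets these participants to active lesions, as a deliberately unfavourable bound. Report by treatment status how many values were observed, carried forward, recovered and imputed, at D14 and D28 separately.

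The cost is a change of wording in the missing-data section and the SAP, and a standard imputation step. Intervals will be slightly wider and the proportion resolved will probably look less favourable. Multiple imputation does not remove the problem if attendance depends on healing, which is why the bound is needed.
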